## Abstract

**Background:**

The Tehran Lipid and Glucose Study (TLGS) is a long term integrated community-based program for prevention of non-communicable disorders (NCD) by development of a healthy lifestyle and reduction of NCD risk factors. The study begun in 1999, is ongoing, to be continued for at least 20 years. A primary survey was done to collect baseline data in 15005 individuals, over 3 years of age, selected from cohorts of three medical heath centers. A questionnaire for past medical history and data was completed during interviews; blood pressure, pulse rate, and anthropometrical measurements and a limited physical examination were performed and lipid profiles, fasting blood sugar and 2-hours-postload-glucose challenge were measured. A DNA bank was also collected. For those subjects aged over 30 years, Rose questionnaire was completed and an electrocardiogram was taken. Data collected were directly stored in computers as database software- computer assisted system. The aim of this study is to evaluate the feasibility and effectiveness of lifestyle modification in preventing or postponing the development of NCD risk factors and outcomes in the TLGS population.

**Design and methods:**

In phase II of the TLGS, lifestyle interventions were implemented in 5630 people and 9375 individuals served as controls. Primary, secondary and tertiary interventions were designed based on specific target groups including schoolchildren, housewives, and high-risk persons. Officials of various sectors such as health, education, municipality, police, media, traders and community leaders were actively engaged as decision makers and collaborators. Interventional strategies were based on lifestyle modifications in diet, smoking and physical activity through face-to-face education, leaflets & brochures, school program alterations, training volunteers as health team and treating patients with NCD risk factors. Collection of demographic, clinical and laboratory data will be repeated every 3 years to assess the effects of different interventions in the intervention group as compared to control group.

**Conclusion:**

This controlled community intervention will test the possibility of preventing or delaying the onset of non-communicable risk factors and disorders in a population in nutrition transition.

**Trial registration:**

ISRCTN52588395

## Background

Iran is an urbanized city-state country in the Middle East Region. It is considered to be a country in nutrition transition [1]. Like most countries that have undergone rapid economic and demographical transition, non communicable diseases, especially cardiovascular disease, are the major cause of mortality and morbidity in Iran with a high prevalence reported [2-5]. Over the years, progress has been made in the treatment of non-communicable disease (NCD) and in the pharmacological control of many risk factors. However, the most cost-effective and sustainable way of controlling these diseases is through alteration of prevalence of risk factors in the population. This can be done through lifestyle changes such as increasing regular physical activity, eating healthily and remaining tobacco-free [6-8].

The Tehran Lipid and Glucose Study (TLGS) is a large scale community based prospective study performed on a representative sample of residents of district-13 of Tehran, capital of Iran. Tehran city covers an area of 1500 sq. kms and consists of 22 districts with a total population of over ten million people. The TLGS first established in 1999 with the aim of determining the prevalence of NCD risk factors [2]. Rationale and design of the TLGS has been published elsewhere in details. [9].

Results from the first phase of the TLGS (cross-sectional study) revealed high prevalence of NCD risk factors. In adults, 78% of men and 80% of women presented at least one NCD risk factor. Prevalence of diabetes mellitus, hypertension, obesity, high cholesterol, low HDL, high triglycerides, and smoking was 10.6, 22.9, 23.1, 23.6, 21.1, 4.2, and 10.6%, respectively. In children and adolescents, two or more NCD risk factors were found in 9% of boys and 7% of girls. Prevalence of hypertension, obesity, high TC, low HDL, and high TGs, was 11.7, 4.3, 5.1, 8.3, and 5%, respectively [2]. Metabolic syndrome was seen is 32% of adults [10] and 10%.of adolescents [11], and Rose angina was reported in 10% (9% in men and 12% in women) of adults ≥ 30 years [5]. The aged adjusted prevalence of CHD based on the presence of any of Rose angina, self reported history of CHD and ECG defined CHD was 21.8% with 22.3 and 18.8% in women and men respectively [5]. The mean percentage values of energy intake derived from carbohydrate, protein, and fat were 57.8 ± 6.9, 11.1 ± 1.8, and 30.9 ± 7.2, respectively [2].

Following baseline collection of data, the intervention phase of the study was designed to improve healthy lifestyle and prevent NCD risk factors. In designing this large study, similar studies in other countries were reviewed. [12-19] Table 1 shows some of the large and well-known interventional studies which were used in designing the intervention program of the TLGS. The aim of this study was to determine the feasibility and effects of lifestyle modification programs designated to prevent NCD risk factors and outcomes in a community in nutrition transition. This paper describes the protocols, design and the methodology of this interventional program.

**Table 1 T1:** Characteristics of large non-communicable disease interventional studies *

**Study (year)**	**Study Population**	**Fields of intervention**	**Method of intervention**	**Follow-up period**	**Sample size**	**Result**
North Karelia (1997–1972)	Karolia state and Finland	Nutrition, Smoking, Low cholesterol and blood pressure	Intervention on nutrition, T.V program, interventions on work, schools, newspaper and posters	20 years (every 5 years)	8746-2312 (25–64 years)	Successful (reduced cholesterol and raised vegetables and fruits)
Singapore (1992–1998)	whole Society	Nutrition, Smoking and physical activity	Teaching and propaganda	6 years	4723 (18–69 years)	Successful in reduce smoking, unsuccessful in reduce cholesterol level
CINDI (1987)	23 European and Canadian countries	nutrition, smoking, physical activity, alcohol consumption and stress	National Changes in food plan, availability of new food patterns			
Eat for life (2001)	Dark-skinned Americans	Nutrition	Phone consulting		861 (18–87 years)	Successful
DISC (2001)	Children of 8–10 years with high serum LDL level	Nutrition	Teaching and consulting	3 years	663 (8–10 years)	Successful

*The above studies are sited in references.

### Research goals

#### Primary

The primary research goal is an evaluation of the feasibility and effectiveness of lifestyle modification interventions in preventing or postponing the development of NCD risk factors and outcomes in a population in nutrition transition.

#### Secondary

Secondary research goals include determining differences in the prevalence of major NCD risk factors and outcomes between intervention and control groups with special focus on angina pectoris, myocardial infarction, cerebrovascular events, diabetes mellitus, hypertension and dyslipidemia.

### Subgroup Research goals

Other research goals include assessing the consistency of the interventions for lifestyle modifications in a population of a developing country in nutritional transition.

#### Study design

The TLGS design has two major components; phase I was a cross-sectional prevalence study of NCD and its associated risk factors implemented from March 1999 to December 2001. Phase II is a prospective follow-up study which has begun from January 2002. Data recollection is designed to be in 3-year intervals.

#### Study population

A total of 15005 individuals aged 3 years and over who were residence of district No.13 of Tehran and were under the coverage of three medical health centers, were selected using multistage cluster random sampling method. All members of each family, including those not having risk factors, were invited for baseline measurements and will be followed every 3 years. A map of areas of intervention and control groups in district 13 is presented in figure 1. District No. 13, one of the 22 districts of Tehran metropolitan city which it is located in the eastern part of the city and covers the area of about 13 sq. kms and is under coverage of Shahid Beheshti University of Medical Sciences and Health Services was selected. Then three medical health centers of overall 20 medical health centers in the district were selected. As a commentary, all medical health centers in this district have the filed data of almost all covered families (over 90%) and enjoy a well-developed framework of experienced health volunteers (Rabet-e Behdasht) who play a crucial role in the recruitment of people in the study and distribution of written educational documents. They help the study personnel to improve the knowledge and attitude of the study population in the intervention area. A complete demographic database of all families in three centers including family dimension, gender, age, and postal address and telephone numbers were extracted from data in medical centers. Based on the given data, every family was contacted, invited, and then recruited to participate in the study. Age distribution and socioeconomic status of the population in district No. 13 is representative of overall population of Tehran (Iran National Census, 1996) [9]. (Table 2)

**Table 2 T2:** Age distribution in study population, Tehran, and Iran urban inhabitants.

Age group (year)	Study population (%)	Tehran urban inhabitants (%)	Iran urban inhabitants (%)
0–9	15	18	22
10–19	22	25	27
20–29	18	19	17
30–39	16	16	14
40–49	11	11	9
50–59	9	6	5
60–69	9	5	6

**Figure 1 F1:**
[figure not shown]
**The minimum and maximum distances between intervention and control groups are 1.5 and 5 kilometers, respectively**. Map of areas of control (C) and intervention (I) groups.

A total of 5630 subjects under coverage of one of the three health centers which is far from two other centers (Figure 1), were considered for lifestyle modification using primary, secondary and tertiary preventions for NCD.

#### Baseline measurements

The following examinations were performed at the beginning of the study and are performed every three years in both intervention and control groups. The workflow is designed according to the WHO stepwise approach to NCD surveillance [20]. Trained social workers visit study participants 2–4 weeks before the examination and explain the process of study. An appointment will be made for the invited family and the date will be confirmed through a phone call 2–5 days before examination, emphasizing the previous instructions including fasting of 12–14 hour before examination. On the day of examination initially the participants are interviewed for obtaining demographic data or updating existing data. Then, the participants are referred to laboratory for blood sampling. For all non- pharmacologically treated diabetic participants aged 20 years and over, an oral glucose tolerance test with 75 gram glucose is performed and a second blood sample is obtained 2 hours after glucose ingestion.

All the families are followed up for every medical situation through an annual phone call and the relevant medical outcomes are recorded. A trained physician performs complementary interview with patient and/or her/his physician and in the case of hospitalization the physician performs a visit to the hospital to collect relevant data from patient records.

### Medical history and clinical examination

All invited participants to the TLGS unit, after signing informed written consent, are referred to trained physicians. The participants are interviewed by trained physicians to obtain past medical history and to complete a 110-item questionnaire regarding familial history of NCD, smoking habits, reproductive history and assessment of physical activity; brief physical examination is performed including anthropometric measurements. Rose angina questionnaire is completed and ECG is taken from individuals over 30 years of age. Trained dietitians collect dietary data in one tenth of the participated family.

The participants remain seated for 15 minutes, then a qualified physician measure blood pressure two times using a standard mercury sphygmomanometer calibrated by Iranian Institute of Standards and Industrial Researches. On the basis of the circumference of the participant's arm a pediatric, regular adult or large cuff is used. The cuff is placed on the right arm, which is at the heart level and inflated in as high rate as possible increments until the cuff pressure is 30 mmHg above the level at which the radial pulse disappeared. There is at least a 30-second interval between those two separate measurements, and the mean of two measurements is recorded as the participant's blood pressure. The systolic blood pressure is defined as the appearance of the first sound [Korotkoff phase 1], and the diastolic blood pressure is defined as the disappearance of the sound [Korotkoff phase 5] during deflating the cuff at a 2–3 mm per second decrement rate.

Anthropometric measurements are taken with shoes removed and the participants wearing light clothing. Weight and height are measured according to the standard protocol. Waist circumference is measured at the level of the umbilicus and hip circumference is measured over light clothing at the widest girth of the hip. Body mass index (BMI) is calculated by dividing the weight in kilograms by the square of height in meters.

### Blood sample collections

A blood sample is drawn between 7:00 and 9:00 a.m. into vacutainer tubes from all study participants after 12–14 hours overnight fast. Two blood samples are taken in a sitting position according to the standard protocol. The blood collected in EDTA containing test tube is used to obtain DNA sample; other sample is centrifuged within 30 to 45 minutes of collection. The derived serum are separated into at least four 1-ml aliquots; One for all biochemical analyses to be done at the TLGS Research Laboratory on the day of blood collection, and three aliquots to be stored in -80°C ultra freezers for future studies. For oral glucose tolerance test 82.5 g glucose monohydrate solution [equivalent to 75 g anhydrous glucose; Cerestar EP, Spain] is administered orally in subjects aged more than 20 years except in diabetics on medication. A second blood sample is taken two hours after glucose ingestion.

### Rose angina questionnaire

Using the Persian translated Rose questionnaire, the history of any chest pain is assessed. Rose angina had been designed by Jeffery Rose for participants who had chest pain during exertion. This pain forces the person to stop and goes away in less than 10 minutes when he/she stops. If present, the pain is situated over anterior or left lateral sternum or radiates to the left arm. Rose questionnaire data are interpreted according to previously published guidelines [21].

### ECG measurements

A 12-lead rest ECG is recorded by two trained and qualified technicians according to a standard recording protocol developed by the School of Public Health, University of Minnesota [22] using a PC-ECG 1200 machine. Two trained physicians code the ECGs independently according to the Minnesota codes using a measuring loupe specially manufactured by University of Minnesota [23]. To assure the quality, a third trained physician recoded 10% of ECGs and all the data are doubly entered and rechecked. Coronary heart disease (CHD) is defined based on Whitehall criteria [23]. The population under study is categorized into three groups of probable CHD, possible CHD and non-CHD on the basis of ECG findings and Whitehall criteria. Any Minnesota codes of 1.1 through 1.2 are considered as probable CHD and codes 1.3, 4.1–4.4, 5.1–5.3, or 7.1 as possible CHD.

### Cigarette smoking status

Different categories of cigarette smoking status are defined according to WHO guidelines [24]. Daily smoker is defined as who smokes cigarettes at least once a day; occasional smoker is who smokes cigarettes but not every day; ex-smoker is formerly daily or occasional smoker who currently does not smoke; and never smoked defined as who never smoked before or smoked too little in the past.

### Physical activity levels

Physical activity level was assessed using Lipid Research Clinic (LRC) questionnaire [25] in the first phase of the TLGS. Since the LRC questionnaire assesses physical activity level of the participant qualitatively and the questions are fully subjective, the derived data were not accurate. So, the Steering Committee of the TLGS replaced the questionnaire by Modifiable Activity Questionnaire (MAQ) [26] and a Persian translated form of that is used to assess physical activity level in the TLGS participants. The questionnaire measures all three forms of activities including leisure time, job, and household activities in the past year.

### Definitions for risk factors

According to the JNC-VI [Joint National Committee] criteria [27], hypertension in adults is defined as mean systolic blood pressure (SBP) ≥ 140 mmHg, mean diastolic blood pressure (DBP) ≥ 90 mmHg, or current treatment with antihypertensive medications either at the time of interview or in the previous one month. Awareness of hypertension reflects any prior diagnosis of hypertension by a physician and is defined positive answer to relevant question at the time of the interview. Blood pressure readings in children and adolescents are evaluated using the guidelines from the 1987 Task force reports [28].

A BMI of 25 to 29.9 kg/m^2 ^in adults is considered as overweight and a BMI equal to or more than 30 kg/m^2 ^is defined as obesity. Obesity and overweight in children and adolescents are defined according to international cut off points for body mass index [29]. Truncal obesity is defined as a WHR more than 0.95 in adult men and more than 0.8 in adult women.

Derived from those of Franklin FA et al. [30] the 95^th ^percentile of serum cholesterol, triglycerides and LDL-C, distributions are used as the cut-points in children and adolescents to assign subjects at different level of cardiovascular risk. The 5^th ^percentile of concentration of serum HDL-C in total population of children and adolescents in each age group and sex are used as cut-off point for the low HDL-C levels [30]. In adults, the desirable level for TC is defined as less than 200, moderate risk as 200–239, and high risk as ≥ 240 mg/dl. For LDL-C the desirable level is defined as <130, moderate risk as 130–159, and high risk as ≥ 160 mg/dl. The desirable level for TGs is defined as <200, moderate risk as 200–400, and high risk as ≥ 400 mg/dl. Serum HDL-C is divided in three levels of risk; <35, 35–59, and ≥ 60 mg/dl [31].

The results of the oral glucose tolerance test of each subject are used to classify glucose metabolism status according to the WHO criteria [32], and subjects were classified according to 2-hour post-load plasma glucose (2 hPG): normal 2 hPG<140 mg/dl, IGT 200>2 hPG ≥ 140, or diabetic 2 hPG ≥ 200 mg/dl.

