### Concomitant conditions

Medical illnesses requiring treatment that could affect implementation of TLGS study protocol are not considered to be important intervening factors. Participants having conditions or illnesses related to risk factor are advised to attend TLGS clinics or visit their own private physicians. All concomitant medical conditions are recorded in yearly telephone calls and outcomes are completely sought. Use of medications, applications of procedures and occurrence of any disease are registered in every 3 year fact-to-face visits.

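### The diabetes definition rests on a 2-hour glucose test that treated diabetics do not take, and no rule says how to count them

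*Protocol article*

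**What the plan says.** All places are in the protocol article.

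- **Definitions for risk factors** bases glucose status on the tolerance test: "The results of the oral glucose tolerance test of each subject are used to classify glucose metabolism status". It goes on: "subjects were classified according to 2-hour post-load plasma glucose (2 hPG", with normal below 140, impaired tolerance from 140 to below 200, and diabetic at 200 mg/dl or above. No medication, prior-diagnosis or fasting-glucose criterion appears.
- **Blood sample collections** says that the glucose solution "is administered orally in subjects aged more than 20 years except in diabetics on medication". **Baseline measurements** seems to intend the same, in unclear wording: "For all non- pharmacologically treated diabetic participants aged 20 years and over, an oral glucose tolerance test with 75 gram glucose is performed".
- The hypertension definition, in the same section as the diabetes rule, has a treatment criterion: "or current treatment with antihypertensive medications either at the time of interview or in the previous one month".
- **Research goals, Secondary** lists diabetes among the conditions to be compared between the arms: "with special focus on angina pectoris, myocardial infarction, cerebrovascular events, diabetes mellitus, hypertension and dyslipidemia". **Biostatistical considerations** plans to estimate diabetes incidence and gives diabetes, impaired tolerance and normal as its example of a multinomial outcome. Those are the three classes of the 2-hour rule.
- **Abstract, Design and methods** includes in the intervention "training volunteers as health team and treating patients with NCD risk factors".
- **Concomitant conditions** says: "Use of medications, applications of procedures and occurrence of any disease are registered in every 3 year fact-to-face visits". **Outcome measurements** describes annual telephone calls and a committee that assigns outcomes by ICD-10.

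**The concern.** A classification rule has to return a class for everyone in the comparison. This one needs a 2-hour value, and the people most certainly diabetic, those already on drugs for it, are the people who do not have one. Someone who develops diabetes and starts medication between two 3-yearly visits arrives at the next visit with no value on the defining variable. An analyst following the text would have to treat that person as missing or as not diabetic, or make up a rule.

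Two things are at stake. The level of diabetes would be understated in both arms. And because treatment can be influenced by the intervention, the cases lost need not be the same share in each arm, so a difference in drug treatment could appear as a difference in disease.

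**Working it through.** The article bases no sample size, power or error rate on the diabetes definition, so there is no planned figure to reproduce. The check shows what the written rule does when the true disease level is the same in both arms.

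**Inputs**

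- True prevalence D = 0.106 in both arms. This is the adult diabetes prevalence given in Background, used here only as a convenient base.
- Share t of diabetics on medication. The article does not give it. Assumed values run from 30% to 60%, separately by arm.

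**Formulas**

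- Treated cases missing, because they have no 2-hour value: counted prevalence = D(1 − t) / (1 − Dt).
- Treated cases counted as not diabetic: counted prevalence = D(1 − t).

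**Understatement within an arm (treated cases missing)**

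- t = 0.4: 0.0636 / 0.9576 = 0.0664, so 1 − 0.0664/0.106 = 37% too low.
- t = 0.5: 0.0530 / 0.9470 = 0.0560, so 47% too low.
- t = 0.6: 0.0424 / 0.9364 = 0.0453, so 57% too low.

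If treated cases are counted as not diabetic, the understatement is simply t, that is 40% to 60%.

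**Comparison between arms, no true difference**

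| Treated share, control / intervention | Counted prevalence, control / intervention (missing) | Ratio, missing | Ratio, counted as not diabetic |
|---|---|---|---|
| 30% / 30% | 7.7% / 7.7% | 1.00 | 1.00 |
| 30% / 40% | 7.7% / 6.6% | 0.87 | 0.86 |
| 40% / 50% | 6.6% / 5.6% | 0.84 | 0.83 |
| 50% / 60% | 5.6% / 4.5% | 0.81 | 0.80 |
| 40% / 60% | 6.6% / 4.5% | 0.68 | 0.67 |
| 50% / 40% | 5.6% / 6.6% | 1.19 | 1.20 |

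The ratio hardly depends on D. For 40% / 50% it is (0.5/0.6) × (0.9576/0.9470) = 0.84, and it tends to 0.83 as D falls. What drives it is the difference in treated share.

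For incidence the same formula applies, with t read as the share of new cases already on drugs at the next visit. The article gives no incidence figure, so that size is not worked out here.

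**With a medication criterion.** Counted prevalence becomes D(1 − t) + Dt = D, so 10.6% in both arms and a ratio of 1.00 whatever the treated shares, provided that medication is recorded completely.

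**The case against.** The other side has a good deal to say.

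1. **No sentence excludes treated diabetics.** The 2-hour rule grades test results, and the people exempted from the test are already called diabetic in the sentence that exempts them. WHO criteria are cited as well. A reader might infer that the plan drops treated cases by rule; it does not say so, and in practice they may well be counted. This stands. The finding is that the written definition leaves them without a class.
2. **Other routes could capture them.** The annual calls, the ICD-10 committee and the 3-yearly medication record could all identify a treated diabetic. But nothing ties any of them to the diabetes definition, and unlinked routes allow two different counts of diabetes. This lowers the cost of the repair but does not remove the gap.
3. **Differential case-finding is not supported.** A reader might infer that the intervention area looks harder for diabetes. The article says that the examinations are made in both groups and that the annual call covers every family. Advice to attend the study clinics or a private physician is not restricted to one arm, and the Clinics section describes diet and smoking advice, not a glucose-lowering drug programme. What remains is that treating patients is listed as an intervention strategy. A lifestyle programme could also reduce drug use, which would reverse the bias.
4. **The base figure is awkward.** If the reported 10.6% includes treated cases, the study already counts them; if not, it is not the true prevalence. That is fair, but the ratios barely depend on it.
5. **Lipids.** A reader might infer that treated lipids are always counted as normal. The article gives risk bands for adults and no binary dyslipidemia definition, and a treated value falls in a lower band only if treatment brings it there. Lower lipids through treatment may also be part of the effect under test, so imputing untreated values would change the question asked.

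**Conclusion.** The point holds as an inconsistency in an outcome definition. The article states a rule, withholds from a known group the test that the rule needs, and handles the same situation differently for hypertension a few lines earlier. That goes beyond detail left to an analysis plan, because the definition that is given fails for part of the population.

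Read literally, it understates diabetes prevalence by about 37% to 57% if 40% to 60% of cases are treated, and it understates incidence by the same mechanism. Bias between arms is conditional: none if the treated shares are equal, a ratio of 0.84 at 40% control against 50% intervention, and 1.19 if those shares are reversed. All treated shares are assumptions. The documents therefore do not support the stronger conclusion that the trial is biased towards a positive result; they show only that the definition does not protect against bias in either direction.

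Severity is moderate. Diabetes is a named secondary comparison, while the sample size rests on cholesterol.

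**What to change.** For the outcome analysis, in both arms and at every examination including baseline, count a participant as diabetic if any of these holds:

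- 2-hour glucose meets the cut-off already stated;
- glucose-lowering medication is recorded at the 3-yearly visit;
- the outcome committee has confirmed diabetes.

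The fasting glucose already measured can be added as a further criterion. Cross-reference Definitions for risk factors, Outcome measurements and Concomitant conditions so that one definition serves prevalence, incidence and the three-class outcome. If practice already counts treated participants, say so there.

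For lipids, state only that lipid-lowering medication counts towards any binary dyslipidemia outcome.

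The cost is a few lines of definition and some derivation code. No new measurement is needed, and who takes the glucose test does not change.
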